### Potential predictive factors collected

Potential candidate variables for the NEUROPACK clinical prediction model have been selected from the existing clinical prediction models for survival.^1 6 13^ Final candidate variable selection will follow assessment of statistical modelling interaction and practicality of collecting variables in a timely fashion at the bedside by clinicians.

### Data collections

The ongoing NET-PACK 3 customised data collection and PICANet data collection for the PIM3 risk of mortality will be the data source for all the candidate variables in the NEUROPACK study. Linkage of individual patient NET-PACK 3 data with the collected neurodevelopmental outcome will be carried out for consented patients only. Pseudonymised data from NET-PACK 3 customised data collection and PICANET will be used for patients who die or for patients who survive and consent for follow-up assessment is not available.

## Primary and secondary outcomes

### Primary outcome

The primary outcome is survival with a good neurodevelopmental outcome at 3 months postevent. Good neurodevelopmental outcome is defined as a Vineland Adaptive Behaviour Scales second edition (VABS-II) score of ≥70.^18^

### Primary outcome assessment

The VABS-II was designed as a caregiver report measure to assess communication, daily living, social and motor domains of adaptive behaviour.^18^ This tool can be used across the entire paediatric age range (0–16 years) and requires a short interview which can be via telephone. VABS-II is sensitive to neurological injury and has been used successfully in paediatric neurocritical care studies.^2^ VABS-II has a normal mean value score of 100 (SD of 15). Good neurodevelopmental outcome is defined as a score of ≥70. Poor outcome is a composite score of VABS-II <70 and death. The chief investigator or the lead research nurse at the Central Research Centre (Birmingham Women and Children’s National Health Service (NHS) Foundation Trust, UK) will conduct all assessments. At the time of outcome assessment, the assessor will remain blinded to the clinical prediction model and component variables.

### Secondary outcomes

Paediatric cerebral performance category (PCPC) and paediatric overall performance category (POPC) at 3 months and change in PCPC and POPC score from baseline.^19^ Survival to PICU discharge and 3 months post-CA.

### Secondary outcome assessment

PCPC and POPC scale can be calculated by a short questionnaire conducted at the 3-month follow-up interview for consented patients. A baseline (pre-CA) PCPC and POPC will also retrospectively ascertained at the 3-month follow-up. PCPC and POPC have been recommended for reporting in all paediatric CA studies. They score 1–6 (1: normal, 2: mild disability, 3: moderate disability, 4: severe disability, 5: vegetative state or coma and 6: death). They provide less detail but correlate reasonably well with VABS II.^20^ This will allow comparison with other CA studies. Good neurodevelopmental outcome will be defined as PCPC score of 1–3 or no change from baseline. Poor outcome will be defined as a score of 4 or more, including death. Three months follow-up time point is chosen following the ILCOR, core outcome set for adults after CA recommendation^21^ and demonstration of minimal change between three and 12-month following CA.^22^

## Statistical consideration

### Data analysis plan

The data will be manually reviewed for errors, missing data and outliers before analysis. Extreme values will be set to missing if they are deemed unlikely, based on their validity range. Descriptive analysis of the data will be reported. Continuous variables will be reported as either median and interquartile range (IQR) or mean and standard deviation (SD) based on the distribution. Categorical variables will be described in numbers, percentages or both.

### Sample size

To reduce problematic bias and improve precision we aim for at least 10 events per variable considered for multivariable modelling.^23^ Following pilot data collection, we calculate 250 CA patients per year are admitted to 27 UK and RoI PICUs, 125 (50%) will survive to PICU discharge and 70 (30%) per year will survive with good neuro-developmental outcome. To test seven variables we estimate a requirement of 70 events (eg, patients with good neurodevelopmental outcome). One hundred per cent of non-survivors will be included (included in PICANet and NET-PACK 3 audit database). We anticipate 80% recruitment and consent rate of remaining survivors. We, therefore, require data collection over an 18-month period to recruit 370 patients. We anticipate that this would ensure successful consent and follow-up of 150 patients, of whom 75 patients are estimated to have a good neurodevelopmental outcome.

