**Methods and analysis:**

A prospective study of children (age: >24 hours and <16 years), admitted to 1 of the 24 participating PICUs in the UK and Ireland, following an OHCA or IHCA. Patients are included if requiring more than 1 min of cardiopulmonary resuscitation and mechanical ventilation at PICU admission Children who had cardiac arrests in PICU or neonatal intensive care unit will be excluded. Candidate variables will be identified from data submitted to the Paediatric Intensive Care Audit Network registry. Primary outcome is neurodevelopmental status, assessed at 3 months by telephone interview using the Vineland Adaptive Behavioural Score II questionnaire. A clinical prediction model will be derived using logistic regression with model performance and accuracy assessment. External validation will be performed using the Therapeutic Hypothermia After Paediatric Cardiac Arrest trial dataset. We aim to identify 370 patients, with successful consent and follow-up of 150 patients. Patient inclusion started 1 January 2018 and inclusion will continue over 18 months.

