### Setting

Patients will be enrolled from 24 PICUs within the UK and RoI. All study sites admit infants and children following CA and routinely submit audit data to the Paediatric Intensive Care Audit Network (PICANet) registry.

### Ongoing PICU registry: PICANet and NET-PACK 3

Since 2002, PICANet has prospectively collected demographic, diagnostic, and interventional data along with PICU survival outcomes for patients admitted to PICUs in England and Wales and now collects data for patients across the UK and RoI.^14^ This includes severity of illness variables to build the Paediatric Index of Mortality (PIM) risk-adjustment models.^15^

PICANet is also conducting an ongoing customised data collection of post-CA management: PICANet Post Arrest Care in Kids (NET-PACK 3) with data definition and data collection form (online supplemental materials 1 and 2). NET-PACK 3 customised data collection includes resuscitation variables available within a few hours of the CA. Data are either collected within 1 hour of admission onto PICU or within 1 hour of the attendance at the patient’s bedside of a specialist paediatric critical care team (eg, a specialised retrieval team travels to another hospital without a PICU). These variables include: (1) attempted bystander cardiopulmonary resuscitation (CPR), (2) duration of CPR, (3) requirement of CPR after arrival at emergency department, (4) number of doses of epinephrine (epinephrine) required and (5) initial presenting cardiac rhythm. These factors were chosen to comply with Utstein style CA reporting guidelines.^16 17^ PICANet collects survival to PICU discharge outcome data for all admissions.

10.1136/bmjopen-2020-037517.supp1Supplementary data

10.1136/bmjopen-2020-037517.supp2Supplementary data

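### The recruitment projection rests on admissions to 27 PICUs although 24 take part, allows no loss after consent, and uses conflicting good-outcome rates; whether 70 events are reached depends on which rate applies

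*Protocol article*

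**What the plan says.** The Sample size section of the protocol article builds its projection in these steps:

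- Admissions: "we calculate 250 CA patients per year are admitted to 27 UK and RoI PICUs".
- Outcomes: "125 (50%) will survive to PICU discharge and 70 (30%) per year will survive with good neuro-developmental outcome".
- Requirement: "To test seven variables we estimate a requirement of 70 events (eg, patients with good neurodevelopmental outcome".
- Consent: "We anticipate 80% recruitment and consent rate of remaining survivors".
- Result over 18 months: 370 patients, with "successful consent and follow-up of 150 patients, of whom 75 patients are estimated to have a good neurodevelopmental outcome".

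Two other places give the number of sites. The Setting section says "Patients will be enrolled from 24 PICUs within the UK and RoI", and the abstract describes children "admitted to 1 of the 24 participating PICUs in the UK and Ireland".

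The Secondary analysis section names refusal of consent, loss to follow-up and exclusion as reasons why survivors may have no score. It gives no rate for any of them.

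**The concern.** There are three problems, all within or bearing on the one Sample size paragraph.

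1. The admission count belongs to 27 units, and the study enrols from 24. The article does not say that the 250 was restricted to the participating units, or that the other three contribute negligible volume.
2. The 80% is labelled a recruitment and consent rate, yet it alone takes survivors to the number consented and followed up. Retention from consent to the telephone interview is in effect set at 100%.
3. The good-outcome rate changes between the start and the end of the paragraph, so a reader cannot tell which one the 75 events should rest on.

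This paragraph is the only justification for the size of the model. The margin between 75 expected and 70 required events is five, so small changes in any input decide whether ten events per variable is available for seven variables.

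**Working it through.** **Inputs.** From the Sample size section: 250 admissions a year, 27 units, 125 survivors a year (50%), 70 good outcomes a year (printed as 30%), 80% consent, 18 months, target 70 events. From the Setting section and the abstract: 24 units. From the Introduction: 250 to 350 admissions a year, and half of survivors with continuing disability.

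**The plan's own figures.**

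- Patients: 250 × 1.5 = 375 (stated as 370).
- Survivors: 125 × 1.5 = 187.5.
- Followed up: 187.5 × 0.80 = 150 (as stated).
- Good outcomes: 150 × 0.50 = 75 (as stated).

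The chain reproduces, but only with all 27 units and no loss after consent.

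**The good-outcome share among survivors.** The paragraph supports three values:

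- 75/150 = 50%, which agrees with the Introduction.
- 70/125 = 56%. As a share of admissions, 70/250 = 28%, not 30%.
- 30%/50% = 60%, if the printed 30% is taken literally.

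With 27 units and no loss these give 75, 84 and 90 events. Only the first matches the stated result.

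**Re-based on 24 units.** Assumption: equal volume per unit.

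- Patients: 375 × 24/27 = 333.3.
- Survivors: 333.3 × 0.5 = 166.7.
- Consented: 166.7 × 0.8 = 133.3.

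The article gives no loss rate, so 0%, 10% and 20% are shown as assumptions:

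| Loss after consent | Followed up | Good outcomes at 50% | at 56% | at 60% |
|---|---|---|---|---|
| 0% | 133.3 | 66.7 | 74.7 | 80.0 |
| 10% | 120.0 | 60.0 | 67.2 | 72.0 |
| 20% | 106.7 | 53.3 | 59.7 | 64.0 |

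**Break-even points for 70 events.**

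- 24 units, 50% share: already short by 70 − 66.7 = 3.3 events.
- 24 units, 56% share: 1 − 70/74.7 = 6.3% loss.
- 24 units, 60% share: 1 − 70/80 = 12.5% loss.
- All 27 units, 50% share: 1 − 70/75 = 6.7% loss.
- 50% share, no loss: the 24 units must take at least 70/75 = 93.3% of the 250 admissions. A proportional share is 24/27 = 88.9%.

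**Accrual time for 370 patients from 24 units.** 250 × 24/27 = 222.2 a year, and 370/222.2 × 12 = 20.0 months.

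**Parameters supported at ten events each.** Before loss, 66.7, 74.7 and 80.0 events support 6, 7 and 8 parameters. At 10% loss, 60.0, 67.2 and 72.0 support 6, 6 and 7.

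**The case against.** A reader might infer that the study will miss its 70 events. The documents do not support that as a flat statement, for four reasons.

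- Only the 50% share falls below 70 before loss. The section also states "70 (30%) per year will survive with good neuro-developmental outcome", and that yearly figure carried through 24 units gives 74.7; the printed percentage gives 80.0.
- The 24/27 scaling assumes equal unit volume. No unit volumes are given, and the three other units may be small.
- The 250 is the low end of the Introduction's range. With 24/27 scaling, a 50% share and no loss, 262.5 admissions a year give 70 events, 300 give 80 and 350 give 93.
- Any specific retention rate is the reviewer's assumption.

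All four stand, and they make the shortfall conditional. They do not repair the stated chain. The section plans on 250 a year from pilot data, not on the wider range. Under proportional scaling at that figure, 370 and 150 are not reached in 18 months whichever good-outcome share is used.

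It can also be said that loss is not ignored. Families are recontacted at 2 months, and survivors without a score are handled by imputation and by best-case and worst-case analyses. The 80% may also already cover survivors who are ineligible, for instance on language grounds. The last point is fair, so no separate deduction for language exclusions is made here. The others reduce loss or test its effect on the model. They do not put a retention rate into the projection.

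Finally, printing 375 as 370 and 28% as 30% is rounding and would not matter alone. The difference between 50% and 56% of survivors is not rounding: over the plan's own 150 it is 75 against 84 events.

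**Conclusion.** The point holds in conditional form. The projection is wrong as written: its admission base is 27 units where the study has 24, it contains no loss after consent, and its good-outcome inputs conflict.

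Assuming proportional unit volume and 250 admissions a year, 18 months yields about 333 patients instead of 370 and about 133 followed up instead of 150, before any loss. Expected good outcomes lie between 66.7 and 80.0 before loss, and between 60 and 72 with an assumed 10% loss. The shortfall against 70 is certain neither way. Before loss it follows only if the 50% share and proportional volume both hold, and then it is 3.3 events, or 9.5 events for each of seven variables (66.7/7). The sensitivity to attrition does not depend on the unit count: with all 27 units and the 50% share, loss above 6.7% is enough to miss the target.

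**What to change.** Rewrite the projection in the Sample size section as follows:

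1. Base it on the 24 participating units, or state the share of the 250 admissions that those units take.
2. Show consent and retention to 3 months as separate factors, with a stated retention assumption.
3. Choose one good-outcome share among survivors and use it throughout, correcting either the yearly 70 with its printed 30% or the final 75 of 150.
4. Report expected patients, follow-ups and good outcomes as a range, with the number of candidate parameters that range supports at ten events each (about 6 to 8 before loss).
5. State that falling below 70 events is conditional on the 50% share and proportional unit volume.

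The cost is wording and a less favourable headline figure. No design change is required. Extending accrual is optional; at the re-based rate, 370 patients would take about 20 months.

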### Statistical methods for developing a prognostic model

We will develop a prognostic model using logistic regression analysis of candidate variables and a good neurodevelopmental outcome as the primary outcome variable. Multiple imputation (using chained equations) will be used for any variables with missing data considered in the model. Auxiliary variables will be used to aid the imputation. The number of imputed data sets used will be equal to the fraction of missing data.^24^

Box 1 lists all candidate variables. Those variables deemed to be clinically important will be forced into the final model. Candidate variables will be retained if they benefit the model. The process will begin by fitting the full model and then performing backwards elimination, with a conservative significance level of 0.157.^25^ For categorical variables, the category with the lowest p value will dictate whether the variable is included in the final model.

Box 1Patient and cardiac arrest characteristics

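### The study is sized for seven variables at 10 events each, but Box 1 offers 15 candidates to the full model; if all 15 enter, the planned events give about 5 per candidate

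*Protocol article*

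**What the plan says.** Four parts of the protocol article bear on this point.

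- **Sample size, the rule:** "we aim for at least 10 events per variable considered for multivariable modelling". The unit is variables considered, not variables retained.
- **Sample size, its application:** "To test seven variables we estimate a requirement of 70 events". The section then expects 370 patients, 150 survivors followed up and 75 good outcomes. The seven variables are not named.
- **Statistical methods for developing a prognostic model:** Box 1 is described as holding all the candidates, and "The process will begin by fitting the full model and then performing backwards elimination", at a significance level of 0.157. Variables judged clinically important are forced in.
- **Potential predictive factors collected:** "Final candidate variable selection will follow assessment of statistical modelling interaction and practicality of collecting variables", the practicality being that of timely collection at the bedside. No target number is given.

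**The concern.** The sample size rests on one criterion, events per variable, which the protocol adopts to limit bias and improve precision. That criterion is applied to seven variables, while the modelling section starts from a list about twice as long. Overfitting depends on everything that is tried, so finishing with seven variables after backward elimination would not bring back 10 events per variable.

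At stake is the stated protection against an overfitted model: unstable selection of variables and, before any correction, predictions that are too extreme. The model is intended to support communication with families and risk stratification after a child's cardiac arrest, so a reader should be able to rely on what the protocol says about its statistical footing.

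**Working it through.** **1. The plan's own figures, from Sample size**

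- Events required: 7 variables × 10 = 70. This matches.
- Patients in 18 months: 250 per year × 1.5 = 375, against 370 stated.
- Survivors followed up: 375 × 0.50 × 0.80 = 150 (148 from 370). This matches.
- Events expected: 150 × 0.50 = 75 (74 from 370). This matches.
- Events per variable for seven: 75/7 = 10.7.

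For seven variables the arithmetic is right.

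**2. Count of Box 1**

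| Group | Variables | Count |
|---|---|---|
| Patient | age; PIM-3 high-risk comorbidity | 2 |
| Arrest and interventions | location; aetiology; CPR duration; CPR continued after emergency department arrival; bystander CPR; initial rhythm; epinephrine doses; vasoactive infusion | 8 |
| Service | inter-hospital transfer; day or night | 2 |
| Physiology | systolic blood pressure; pupils; lactate | 3 |
| **Total** | | **15** |

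**3. Events per candidate if all 15 enter**

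- On expected events: 75/15 = 5.0.
- On required events: 70/15 = 4.7.
- Good outcome among survivors is 50% in the last step, but the annual figures ("125 (50%) will survive to PICU discharge and 70 (30%) per year will survive with good neuro-developmental outcome") imply 70/125 = 56%. Using 56%: 150 × 0.56 = 84 events, and 84/15 = 5.6. The conclusion is unchanged.
- Events needed for 10 per candidate: 15 × 10 = 150, twice the 75 expected. At the stated yield that is 370 × 150/75 = 740 patients, or 36 months.

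**4. Illustration of the consequence (rests on an assumed R²)**

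The protocol gives no R², so a range is assumed. The analysed number is taken as 370 × 0.50 = 185 deaths plus 150 followed-up survivors, n = 335, with 75/335 = 22.4% events. The standard relation between sample size n, number of parameters p and expected shrinkage S is

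n = p / [(S − 1) × ln(1 − R²cs/S)],

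where R²cs (Cox-Snell) is Nagelkerke R² times its maximum, which is 0.655 at this event proportion. Solving for S at n = 335:

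| Assumed Nagelkerke R² | S, 7 parameters | S, 15 parameters |
|---|---|---|
| 0.15 | 0.83 | 0.70 |
| 0.25 | 0.90 | 0.80 |
| 0.35 | 0.93 | 0.86 |
| 0.50 | 0.95 | 0.90 |

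For S = 0.9 at R² = 0.25, seven parameters need about 350 patients and 15 need about 750. At R² = 0.50, 15 parameters need about 332, which the planned sample meets.

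**The case against.** **The list may be trimmed before modelling.** Potential predictive factors collected speaks of a final selection still to come, and the modelling section never gives the size of the full model. One of the two selection criteria, bedside practicality, needs no outcome data. This stands in part: the figure of 5 is conditional on all 15 entering. It does not rescue the figure of 10, because nothing says that the selection yields seven, Box 1 is presented as the whole candidate set, and the other criterion is statistical and undefined.

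**Bootstrap and shrinkage deal with overfitting.** The protocol plans optimism correction, uniform shrinkage of the coefficients and re-estimation of the intercept. These are aimed at over-extreme predictions and reduce the harm. They do not make the stated events per variable true, and a uniform factor does not stabilise which variables are selected.

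**Stronger readings that the protocol does not support.** A reader might infer that any trimming would be left out of the bootstrap. The internal validation section says that each bootstrap model is developed in the same way as the original, so repetition of this step is unstated rather than excluded. A reader might also infer that fractional polynomials necessarily add parameters. The protocol lists single powers and requires p<0.001 to depart from linearity; one chosen power replaces the linear term. The search uses some flexibility, but extra coefficients are not established.

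**Conclusion.** The point holds as an internal contradiction. The protocol promises at least 10 events per variable considered, sizes for seven, and then presents 15 candidates to a full model. If all 15 enter, the expected figure is about 5 per candidate (5.0 on 75 events, 4.7 on 70), half of what is stated.

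The count and the ratio come from the protocol alone; the only condition is that Box 1 is not reduced first. The shrinkage values are illustrative and depend on the assumed R²: 0.70 to 0.86 with 15 parameters against 0.83 to 0.93 with seven for R² of 0.15 to 0.35, and about 0.90 with 15 if R² is 0.50. It would therefore go too far to infer that the final model must be badly overfitted. What is wrong is the stated justification, which the plan as written does not deliver.

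**What to change.** Before any outcome data are examined, do one of the following.

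- **(a)** Name seven candidate parameters, chosen on clinical grounds and bedside practicality, and reduce Box 1 to them. The 70-event requirement then stands as written.
- **(b)** Keep all 15 and restate Sample size as about 5 events per candidate, relying openly on the planned optimism correction and shrinkage.

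In either case, state that the selection described under Potential predictive factors collected is made blind to outcome, or that any outcome-based screening is repeated within each bootstrap sample.

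The cost is wording in the protocol or analysis plan. The price of (a) is fewer candidates; the price of (b) is a less favourable stated figure. Option (a) depends on timing, since a pre-specified choice cannot be recovered once outcomes have been seen.
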